#### Secondary outcome measures

Secondary outcome measures will be measured using both validated and self-constructed questionnaire items. An overview of these items is shown in the online supplementary material S2. Secondary outcome measures include the following:
*Appreciation of the information provision strategy used and preferences regarding the approach used to inform relatives at risk*: This will be evaluated in both probands and relatives using self-constructed items on a 5-point Likert scale (1 = ‘Totally disagree’ to 5 = ‘Totally agree’) in a questionnaire (probands: five items, range 5–25; relatives: six items, range 6–30). Probands will be asked to answer an additional self-constructed item during the structured telephone interview about whether they would have preferred to inform their relatives differently. Two additional self-constructed items will be administered in the intervention group to assess decisional conflict in probands, including whether probands thought it was difficult to choose to inform their relatives themselves or have them informed by the counsellor, and whether they were satisfied by their decision, on a 5-point Likert scale (1 = ‘Totally disagree’ to 5 = ‘Totally agree’; range 2–10). Probands will be asked to fill out these items at T1. At T2, a self-constructed item will be administered to assess whether their opinion regarding the approach used has changed. The questionnaire for relatives also includes a self-constructed item on how they were informed (ie, by whom they were informed and what information was provided). Finally, probands (at T1 and T2) and relatives will be asked whether they visited the website www.erfelijkehartziekten.nl and, if yes, how they evaluated the website, using four self-constructed items on a 5-point Likert scale (1 = ‘Totally disagree’ to 5 = ‘Totally agree’; range 4–20).
*Impact on family communication*: To assess the impact of the tailored approach versus the usual care approach on family functioning, probands (at T1 and T2) and relatives will be asked to fill out an adapted version of the Openness to Discuss Cancer in the Family (ODCF) scale, which assesses communication about genetic risks within families with nine items on a 5-point Likert scale (1 = ‘Totally disagree’ to 5 = ‘Totally agree’; range 9–45).^34^ Psychometric characteristics of the original ODCF scale are satisfactory.^34^ In addition, a self-constructed item will be administered asking about the nature of regular communication with relatives and whether probands and relatives experienced changes in their relationships with relatives as a consequence of the information provision process.
*Impact on psychological functioning*: To assess the impact on psychological functioning, two validated questionnaires will be administered in probands (at T1 and T2) and relatives. Participants will be asked to fill out an adapted version of the Cancer Worry Scale (CWS).^35^ The CWS was developed and validated in Dutch patients with hereditary types of cancer.^35^ Because it was validated in a Dutch patient population and is previously used in a genetic patient population, it was considered the most appropriate scale for this randomised controlled trial. The CWS consists of eight items on a 4-point Likert scale (1 = ‘Almost never’ to 4 = ‘Almost always’; range 8–32). Psychometric characteristics of the CWS have been assessed in a sample of breast cancer survivors, and support its reliability and validity.^35^
In addition, the Hospital Anxiety and Depression Scale (HADS) will be administered to assess whether participants experience anxious or depressed feelings after being informed about the hereditary disease.^36^ The HADS contains two 7-item subscales on a 4-point Likert scale with diverse answer options that assess both anxiety and depression with a score range of 0–21. Psychometric characteristics of the HADS were assessed as good.^36^

10.1136/bmjopen-2018-025660.supp2Supplementary data

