### Objectives

The primary aim of this randomised controlled trial is to assess whether uptake of genetic counselling and testing of relatives at risk of an ICC will be increased by using a tailored approach to information provision for relatives, instead of usual care (ie, the family-mediated approach). Secondary objectives are to evaluate how such a tailored approach is appreciated by both probands and relatives as compared with usual care. In addition, this study aims to assess the perceived impact on family relationships and psychological functioning of both probands and relatives. The protocol presented here has been described based on the ’Standard Protocol Items: Recommendations for Interventional Trials (SPIRIT) statement.^31^

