##### Intervention group

In the intervention group, a tailored approach to informing relatives at risk will be provided. In this approach, probands with a likely pathogenic or pathogenic variant will discuss with the genetic counsellor which relatives are at risk of inheriting the familial variant. They will then be asked which of these relatives they prefer to inform themselves at first using a family letter written by the genetic counsellor, and which relatives they prefer to be directly informed by the genetic counsellor with a similar family letter. This will be discussed during routine post-test counselling. In both cases, after 1 month, the genetic counsellor will send the family letter directly to all relatives at risk for whom the proband has provided consent to contact. The proband will be asked to provide contact details of these relatives.

The family letter is standardised for all three participating centres. For the intervention group, the letter also includes a link to a website specifically designed for this study where relatives can find additional information (www.familieleden.erfelijkehartziekten.nl). The information on this website will be tailored to relative’s situations (ie, specified for disease-type, hospital, parenthood, whether relatives have a desire to have children in the future and which information relatives prefer to receive) by asking them to fill out a short questionnaire on their first visit to the website.

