#### Measurement time points

For secondary outcome measures, participating probands will be asked to complete a questionnaire 1 month after receiving the genetic test result (T1) and to complete a second questionnaire 9 months after the test result (T2). Before T1 and T2, a short structured telephone interview will be conducted about participant’s knowledge of which relatives are at risk of ICCs and which relatives are informed, because these items are expected to be too complex to answer in a questionnaire.^33^ Participating relatives will complete one questionnaire after attending genetic counselling.

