### Data analysis

#### Statistical analysis

Sociodemographic, clinical, psychosocial and personality variables will be analysed using descriptive and frequency statistics. An intention-to-treat approach will be used. SPSS V24.0 will be used to perform statistical analyses.^44^ An α level of p<0.05 will be used. Analysis of variance and χ tests will be used to assess differences (1) in sociodemographic, clinical and psychological characteristics between the intervention and control groups and (2) in participants and non-participants, as appropriate. Descriptive and frequency statistics will be used to describe the primary outcomes: (1) uptake of genetic counselling and (2) uptake of predictive DNA testing. Logistic regression analysis will be conducted to assess differences between the intervention and control groups on the primary outcomes, with the randomisation group as the main exploratory variable. Two logistic regression models will be used, with the first model including only the randomisation group and the second model also including the potential covariates (ie, sociodemographic, clinical and psychological variables). Multilevel analyses will be performed to assess whether the randomisation group, that is, the independent variable, has an impact on family and psychological functioning, that is, the secondary outcome variables. The two measurement time points in probands will be treated as nested within probands. To prevent influence of potential confounding factors, multilevel analysis will be adjusted for covariates as well. Participant appreciation of the approach used will be described using frequency statistics.

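### The full proband appreciation scale appears to be given only at T1, about when the direct letters go out, and a comparative objective is analysed by frequencies alone

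*Protocol article*

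**What the plan says.** Four places in the protocol article bear on this.

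- **Objectives.** One secondary aim is to "evaluate how such a tailored approach is appreciated by both probands and relatives as compared with usual care". This is worded as a comparison between arms.
- **Intervention group.** Probands choose at post-test counselling whom they will inform and whom the counsellor will inform. Then: "In both cases, after 1 month, the genetic counsellor will send the family letter directly to all relatives at risk", limited to relatives whom the proband agrees to have contacted.
- **Measurement time points and Secondary outcome measures.** T1 is 1 month and T2 is 9 months after the result. Probands have five appreciation items (range 5–25), and in the intervention arm two further items on their decision. The text continues "Probands will be asked to fill out these items at T1", and the next sentence gives T2 a single item on change of opinion. A telephone item asks whether probands would have preferred to inform relatives differently. Relatives answer six appreciation items (range 6–30) once, after counselling.
- **Statistical analysis.** "Participant appreciation of the approach used will be described using frequency statistics". A multilevel analysis by randomisation group is named for family and psychological functioning only.

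**The concern.** Direct contact by the counsellor is a central part of the tailored approach. A proband who scores the approach at 1 month is scoring it at about the moment the letters leave, before relatives can have reacted. The Introduction itself raises the possibility that active contact could strain family relationships or distress probands and relatives, so the proband's opinion after contact is the more informative one. A single item on whether opinion has changed does not give a T2 score that can be set against the T1 score or against the control arm.

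The second part concerns the analysis. The aim is a comparison with usual care, but the method named for it is descriptive. The trial could then report two sets of frequencies without saying how large the difference is or how uncertain it is. At stake is the evidence on whether probands find the approach acceptable, which readers will want beside the uptake result.

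**Working it through.** **1. Timing.** Months counted from the proband's test result, as the sections give them:

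| Event | Month | Section |
|---|---|---|
| Post-test counselling, choice of who informs whom | about 0 | Intervention group |
| Counsellor mails relatives directly | after 1 | Intervention group |
| T1: proband appreciation items | 1 | Measurement time points; Secondary outcome measures |
| T2: one change-of-opinion item | 9 | same |

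T1 and the mailing share the same nominal time. The 8 months between them and T2 (9 − 1 = 8), when probands can see the effect of direct contact, have no repeat of the scale.

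**2. Is the full scale really confined to T1?** The sentence that fixes T1 directly follows the two decision items, so it could refer to those alone. Two features of the text favour the wider reading. The T2 item on change of opinion presupposes an earlier rating of the approach. And where the article wants a measure at both times (the website items, family communication, psychological functioning), it says so explicitly; it does not for the appreciation items. Hence the scale appears to be given in full only at T1.

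**3. Objective against analysis.** Same aim, two sections: Objectives asks for a comparison with usual care; Statistical analysis names frequencies. The same paragraph gives the other secondary outcomes a model by randomisation group. The article thus states a descriptive method for this aim; it has not merely left the method to another document.

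**4. What an estimate could deliver.** The number of probands comes from Sample size calculation, and its figures reproduce: 50% against 65%, two-sided 5%, 80% power, pooled variance and no continuity correction give 170 per group, 340 in all; 340 / 4 = 85 probands; 85 / (0.20 × 0.70 × 0.80) = 758.9, that is 759 approached. The article gives no SD and no target difference for the appreciation score, so the results below are in SD units (normal approximation, 1:1 allocation).

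- All 85 answer, 42.5 per arm: standard error √(2/42.5) = 0.217 SD; 95% interval ±1.96 × 0.217 = ±0.43 SD; detectable difference at 80% power (1.96 + 0.84) × 0.217 = 0.61 SD.
- Assumed 20% of questionnaires not returned, 34 per arm: √(2/34) = 0.243 SD; ±0.48 SD; 0.68 SD.

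**5. Family and psychological outcomes.** If a model reported one group effect averaged over T1 and T2, its z-value relative to a T2-only contrast would be ((1 + k)/2) / √((1 + r)/2). Here k is the T1 effect as a share of the T2 effect and r the T1–T2 correlation. Take an effect with 80% power at T2 alone (z = 2.80), power Φ(2.80 × ratio − 1.96), and assumed r from 0.4 to 0.8:

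| k | Power of the averaged effect |
|---|---|
| 0 (nothing at T1) | 39% to 31% |
| 0.5 | 71% to 60% |
| 1 (equal effects) | 92% to 84% |

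The first row is the worst case; in the last row averaging gains power. The article fixes neither k nor the form of the model.

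**The case against.** The strongest reply is that the plan collects more than the T1 scale. There is a T2 item on change of opinion, well after the mailing, and a telephone preference item; interviews precede both T1 and T2, although the article does not say at which one this item is asked. Relatives, who are half of the objective, rate the approach after counselling. Both arms complete the scale, so frequencies can be tabulated by arm, and describing a self-constructed secondary scale is a legitimate choice. The arms also diverge before the mailing, through the joint choice of who informs whom and the letter with the tailored website, so a T1 score does reflect part of the intervention. The article does not settle whether relatives assigned to the counsellor get a letter earlier than 1 month.

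Much of this stands, and it rules out some tempting readings. A reader might infer that appreciation is never measured after T1, that the arms are never compared, or that the secondary objectives go unanswered. The text supports none of these. A reader might also infer that T1 and T2 are pooled for family and psychological outcomes and that an effect is therefore diluted towards zero. The article says only that the time points are nested within probands. It neither states an averaged effect nor excludes a group-by-time term, which a statistical analysis plan would commonly settle.

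What the reply does not remove: a change item and a single preference item do not yield a T2 score on the 5–25 scale; only relatives who attend counselling are surveyed; and frequencies by arm are not an estimate of a difference. An earlier letter to some relatives would not alter the fact that the 1-month mailing to the others coincides with T1.

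**Conclusion.** The point holds in a limited form. For probands, the full appreciation scale appears to be given once, at about the time of direct mailing, and T2 has one change item instead of a repeat. For probands and relatives alike, an aim stated as a comparison has an analysis with no stated between-arm estimate. This weakens the answer to one secondary objective and does not touch the primary outcomes.

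The conclusion rests on reading the T1 sentence as covering the five appreciation items, and on taking the 1-month mailing and T1 as roughly simultaneous. The precision figures (±0.43 to ±0.48 SD) assume 85 or 68 responding probands and a normal approximation. They show that an interval is worth reporting and that only a difference of about 0.6 to 0.7 SD would be detected with 80% power. The 31% to 39% power for family and psychological outcomes is a worst case under assumptions the article does not make, and is no part of the finding.

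**What to change.** 1. Repeat the five proband appreciation items in the existing T2 questionnaire, in both arms, for probands who have not yet reached T2. Keep the change-of-opinion item. The two decision items need not be repeated: they concern a choice made at post-test counselling.
2. In Statistical analysis, add to the frequencies a between-arm difference in appreciation score with a 95% confidence interval: at T1 and T2 for probands, and from the single questionnaire for relatives, allowing for clustering of relatives within families.
3. State in Secondary outcome measures which items the T1 sentence covers.
4. As a reasonable addition, report the T2 group contrast from the multilevel model for the family and psychological outcomes.

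The cost is five extra items in a questionnaire already planned, an amendment to that questionnaire, and a few lines of analysis text; no extra visits or participants. Probands already past T2 would have T1 scores only. The article reports 68 probands randomised but not how many had passed T2, so the size of that loss is unknown, and the T2 comparison should state how many probands it includes.

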### Participants’ characteristics

To assess whether randomisation succeeded and whether characteristics of participating probands and relatives have influenced the primary and secondary outcome measures, sociodemographic and clinical factors will be collected, including gender, education level, ethnicity, living situation and parenthood, family history and the diagnosis of the probands at T1. Relatives will additionally be asked what their degree of kinship is with the proband.

For the same reason, psychosocial and personality factors will be assessed in both probands (at T1) and relatives. Coping style will be assessed by using the shortened version of the Threatening Medical Situations Inventory (TMSI).^37 38^ The TMSI assesses a ‘monitoring’ versus ‘blunting’ coping style related to a medical threat, and it was previously evaluated in an oncogenetic patient population.^37 39^ The shortened version of the TMSI contains two subscales, both consisting of six items on a 5-point Likert scale (1 = ‘Totally not applicable’ to 5 = ‘Totally applicable’; range 6–30). Reliability and validity are satisfactory.^37 38^ The Trait subscale of the State Trait Anxiety Inventory (STAI) will be administered to assess trait anxiety in both probands and relatives.^40^ The STAI is frequently used in research settings and consists of 20 items on a 4-point Likert scale (1 = ‘Not at all’ to 4 = ‘Very much so’; range 20–80).^40^ The reliability and validity for the Dutch translation of the STAI are assessed as good.^41^

Self-efficacy and perceived motivators and barriers regarding informing relatives at risk will be assessed using an adapted version of the ‘motivation’ and ‘self-efficacy’ subscales of the Informing Relatives Inventory (IRI).^42^ The IRI was developed and evaluated in an oncogenetic patient population, and showed satisfactory reliability and validity.^42^ The ‘motivation’ subscale consists of 30 items on a 5-point Likert scale (1 = ‘No role’ to 5 = ‘A large role’; range 30–150), and the ‘self-efficacy’ subscale consists of 7 items on a 4-point Likert scale (1 = ‘Not sure at all’ to 4 = ‘Very sure’; range 7–21). Probands will also be asked to answer a self-constructed item during the telephone interviews regarding whether relatives were informed and whether probands intended to inform (remaining) at-risk relatives.

Risk perception regarding the risk of relatives carrying the variant and developing the disease will be assessed by using self-constructed items. These items ask participants to rate the perception of the risk of relatives carrying the variant and developing the disease on a scale from 1 (lowest risk) to 10 (highest risk) as well as from 0% (lowest risk) to 100% (highest risk).

Health literacy—defined as the ability to obtain, process and understand basic health information and services—will be assessed in probands and relatives using the items on the ‘functional health literacy’ and ‘communicative health literacy’ subscales of the 3HL questionnaire.^43^ Both subscales contain five items on a 4-point Likert scale (1 = ‘Never’ to 4 = ‘Often’; range per subscale 5–20). The reliability for both scales was assessed as high and the validity as satisfactory.^43^

### Sample size calculation

The study aims to detect a difference of 15% in uptake of genetic counselling by relatives between the control (usual care, 50%) and intervention groups (tailored approach, 65%). Assuming a two-sided 5% significance level and a power of 80%, 340 relatives (170 in each group) would be required to participate in this study. On average, six relatives per proband are at 50% risk of inheriting the variant, including children and adults.^9^ With a conservative estimate of four eligible adult relatives per proband at risk, 85 probands with an ICC and an identified likely pathogenic or pathogenic (class 4 or 5) variant will need to be included in this study to reach 340 relatives. A likely pathogenic or pathogenic variant is found in, on average, 20% (lower margin) of all probands with a suspected ICC. With an expected response rate of 70% and a drop-out rate of 20%, approximately 759 probands will be approached to participate in the study.

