#### Randomisation

Prior to receiving their test result, probands with an ICC in whom a likely pathogenic or pathogenic variant is identified will be randomly assigned to either the intervention or control group. Block randomisation will be used, with variable blocks ranging from size two to six. Randomisation will be stratified for gender, disease type (cardiomyopathies or primary arrhythmia syndromes) and hospital. To ensure allocation concealment, computer software will be used for randomisation, with an allocation rate of 1:1.^32^ Relatives of probands included in the study will be assigned to the group to which the proband was assigned.

Neither participants nor genetic counsellors will or can be blinded for group assignment. The executing researcher also cannot be blinded because of slight differences between the questionnaires administered in the intervention and control groups. Part of the outcome data will be collected using telephone interviews. To minimise bias, these interviews will be conducted by a research assistant following a structured script.

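### The 80% power claimed for 340 relatives assumes independence, but relatives are allocated by family, so 340 relatives in 85 families have less than 80% power.

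*Protocol article*

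**What the plan says.** Under Sample size calculation, the protocol article targets a rise in uptake of genetic counselling from 50% to 65%: "Assuming a two-sided 5% significance level and a power of 80%, 340 relatives (170 in each group) would be required". It then converts relatives to families: "With a conservative estimate of four eligible adult relatives per proband at risk, 85 probands" are needed to reach 340 relatives. The four adults are set against a larger family average: "On average, six relatives per proband are at 50% risk of inheriting the variant, including children and adults". The remaining steps allow for variant yield (20%), response (70%) and drop-out (20%), which leads to about 759 probands approached. No ICC or design effect is mentioned.

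Under Randomisation, the proband is the unit allocated, 1:1: "Relatives of probands included in the study will be assigned to the group to which the proband was assigned". Under Primary outcome measures, uptake is counted in relatives against all eligible at-risk relatives in the pedigrees. Eligible children are included: from age 10 for cardiomyopathies and, for some arrhythmias, from birth.

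Under Statistical analysis, the primary outcomes are compared by logistic regression on randomisation group, with and without covariates. No family term is stated. Multilevel analysis is described for the secondary outcomes, and the nesting named there is time points within probands.

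**The concern.** Relatives in one family share a proband, a route of information, a disease and a trial arm. The Introduction itself attributes poor uptake largely to causes that sit with the proband, such as disengagement from relatives, grief, or difficulty in conveying complex information. These act on all of a proband's relatives at once, so zero within-family correlation is hard to defend. A sample size that treats the relatives as independent then overstates the information in the trial.

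Two readings of the result are at stake. If the analysis accounts for families, a non-significant result could be taken as coming from an 80%-powered trial when the real power was lower. If the logistic regression is run as described, with no family term, the nominal 5% level is exceeded and a positive result is less secure than it looks.

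**Working it through.** **Inputs.** From Sample size calculation: p1 = 0.50, p2 = 0.65, two-sided 5%, power 80%, 340 relatives, four per proband (six on average with children), 85 probands. From Randomisation: allocation by proband, 1:1. Assumed, because the documents give neither: ICC of 0.05, 0.10, 0.20 or 0.30, and a family-size coefficient of variation (CV) of 0 or 0.5.

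**Step 1: reproduce the plan's figure.** With mean proportion 0.575,

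n per arm = [1.96·√(2·0.575·0.425) + 0.8416·√(0.50·0.50 + 0.65·0.35)]² / 0.15² = (1.3702 + 0.5816)² / 0.0225 = 169.3, so 170.

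Power at 170 per arm is 80.2%. The other sums also reproduce: 340/4 = 85, and 85/(0.20 × 0.70 × 0.80) = 759. The stated 340 is therefore the independent-subjects figure with a design effect of 1, and no inflation is hidden in it.

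**Step 2: allow for families.** Design effect DE = 1 + ((1 + CV²)·m − 1)·ICC, which is 1 + (m − 1)·ICC for equal families. Effective n per arm = (85·m/2)/DE. Power = Φ[(0.15·√n_eff − 1.3702)/0.6910]. For example, with m = 4 and ICC 0.10: DE = 1.30, n_eff = 170/1.30 = 131, and power = Φ[(0.15·√130.8 − 1.3702)/0.6910] = 69%. The detectable difference is the d that gives 80% power against 50% at the same n_eff.

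| ICC (assumed) | m = 4: DE | n_eff per arm | Power, equal families | Detectable difference | Power, CV 0.5 | m = 6: DE | n_eff per arm | Power, equal families | Detectable difference | Power, CV 0.5 |
|---|---|---|---|---|---|---|---|---|---|---|
| 0.05 | 1.15 | 148 | 74% | 16 points | 73% | 1.25 | 204 | 87% | 13.7 points | 85% |
| 0.10 | 1.30 | 131 | 69% | 17 points | 66% | 1.50 | 170 | 80% | 15.0 points | 76% |
| 0.20 | 1.60 | 106 | 60% | 19 points | 55% | 2.00 | 127.5 | 68% | 17.2 points | 62% |
| 0.30 | 1.90 | 89 | 53% | 20 points | 47% | 2.50 | 102 | 58% | 19.1 points | 51% |

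The m = 6 columns use 85 × 6 = 510 relatives. There, power stays at 80% up to an ICC of about 0.10 for equal families, or about 0.08 with CV 0.5. At m = 4, rounding 169.3 up to 170 absorbs an ICC of only (170/169.3 − 1)/3 ≈ 0.001, and at ICC 0.02 power is 78%.

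**Step 3: the test as described.** The powers above belong to a test that accounts for families. For a logistic regression without a family term, the true type I error is about 2·[1 − Φ(1.96/√DE)]. At m = 4 this is 6.8, 8.6, 12.1 and 15.5% at ICC 0.05, 0.10, 0.20 and 0.30. The chance of a significant result at the 15-point effect is then about 78, 77, 75 and 73%, which looks close to the plan but is obtained at an inflated error rate.

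**The case against.** The best counter-argument is that four relatives per family is deliberately cautious. The primary-outcome denominator includes eligible children, the stated average is six, and with 510 relatives in equal families the trial reaches 80% power or more up to an ICC of about 0.10. This stands in part. A reader might infer that the 15-point difference is out of reach, or that real power lies between 50 and 75%. The documents do not support either flat statement, since over the assumed values power runs from 47 to 87%. But the margin is not offered as a clustering allowance, the Abstract fixes the total at 340 relatives, and some of the six may be children under the age limit. The margin also relies on children showing the same effect as adults, and it is used up at moderate ICCs.

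A second argument is that a separate analysis plan may specify a clustered analysis. It may, and a reader should not conclude that families will be ignored in the final analysis. That would protect the type I error but would not restore power. The sample size itself is stated in full and reproduces with no inflation.

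A third is that the ICC is unknown. That is true, and it is why a range is shown. It does not justify a value of zero.

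**Conclusion.** The concern holds in this form. The arithmetic in the article is correct, and the fault is an omitted design assumption. For the stated 340 relatives in 85 families, power at a true two-sided 5% level is below 80% for any positive ICC beyond the trivial rounding slack: 74 to 53% over assumed ICCs of 0.05 to 0.30 with equal families, and lower if family sizes vary. If more relatives count, up to an average of six, the conclusion is conditional. The claim is met at low ICCs and missed at higher ones (87 to 58% for equal families, 85 to 51% with CV 0.5). The sizes rest on assumed values of ICC and CV. That the stated figure contains no clustering allowance does not depend on them.

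**What to change.** Keep 85 probands. In Sample size calculation, replace the 80% claim with:

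- the design effect 1 + ((1 + CV²)·m − 1)·ICC, with the assumed ICC range (for example 0.05 to 0.30) and family-size CV stated;
- the effective sample size, power for 15 points, and difference detectable with 80% power, for m = 4 and m = 6 side by side.

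In Statistical analysis, specify a family-clustered model for both primary outcomes, either GEE or mixed-effects logistic regression, in place of the plain logistic regression, so that the restated power belongs to the test used. Report the observed ICC with the results, so that a null finding is read against the precision actually achieved.

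The cost is a less favourable power figure and slightly more analysis work. No extra participants are asked for. Restoring 80% power with families of four would take 98, 111, 136 or 162 families at the four ICCs, and Trial status reports 68 probands already randomised, so restating the claim is the proportionate step.
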